### Study implementation

#### Data management

The Cochlear P-IROS registry is managed by an experienced, third-party database service provider based in Gembloux, Belgium. The data is stored centrally in an externally hosted, electronic data capture (EDC) platform that is compliant with the standards of the International Conference on Harmonisation – Good Clinical Practice (ICH-GCP) and the US FDA-21-Code of Federal Regulations-Part 11 (FDA-21-CFR-part-11) [52-54]. The Cochlear P-IROS registry protocol adheres to published guidelines for the design and implementation of patient-outcomes registries [33,55]. The Cochlear P-IROS electronic, web-based platform is currently available in five languages; English, Mandarin, Korean, Japanese and Russian. The minimum hardware and software requirements for implementation of the registry include having an internet connection allowing normal and secured communications as well as Adobe Reader Version 8.0 or higher installed (Note: Safari 5.1 or later requires Adobe Reader 10.1.4 or higher.)

#### Data privacy and intellectual property

All clinics will have ownership rights for their site’s data and the flexibility to operate under their own local processes or regulations around data collection, privacy and maintenance of patient records. In Australia, all participating clinics must obtain ethical approval for the Cochlear P-IROS from a legislated Human Research Ethics Committee (HREC), who will assess the study’s protocol and documents for breach of privacy standards. Under the *Australian Privacy Act*, the data collected and stored by the Cochlear P-IROS registry is not classed as, “personal information”, as a patient’s identity is preserved within the database, i.e., no identifiable personal data is collected in any of the evaluation forms administered as part of the study. The Cochlear P-IROS registry is also listed on the Australia New Zealand Clinical Trials Registry, a public database for clinical research in humans that is globally recognised [56].

#### Electronic case report forms

The logical framework of the Cochlear P-IROS registry is set-up as a series of evaluation tools in the format of eCRFs that must be completed through data entry via the electronic platform according to the study’s evaluation schedule. The evaluation schedule highlighting the required and optional assessments is illustrated in Table 1. Paper copies of the eCRFs may also be downloaded and printed from the study platform at any time, ultimately for completion, and storage, ideally in the patient’s clinic file, until data entry online can be undertaken for electronic data capture.

To date, the case-report forms for patients have been translated into 22 languages spoken in China, Japan, Korea, India, Middle East, Taiwan, Turkey, South Africa, South East Asia, Europe and South America and Russia.

#### Data entry

The Cochlear P-IROS registry may complement management of patients at clinics including their routine clinical follow up. A clinician or another approved person at the clinic could enter the data into the Cochlear P-IROS platform. Investigators participating in the registry will have access to real-time patient data updates as well as automated summary reports through the use of their confidential, system-allocated password.

For investigators, automated email reminders notifying follow-up times for individual patients will be sent two months before the evaluation is due. If participating families wish to opt-out of the study, completion of an End of Study form will be required.

For parents/caregivers who have elected and agreed on the patient informed consent form to respond directly on-line, an automated email reminder will be sent two months prior to the next follow-up evaluation for their child, and on the day of the scheduled follow-up. If a parent/caregiver do not respond and complete the recommended evaluations for a particular time-point, the clinician will be subsequently notified by email. A notification will be sent to the clinician, once the parent has completed their data entry for that time-point.

#### Data outputs

The Cochlear P-IROS web interface facilitates centre-specific, automated summary reports on the number of patients recruited to-date, their age at implantation, number and types of implants and outcomes (i.e., mean CAP-II, mean SSQ-P and mean CuHI-QoL). Country and global summaries across these measures are also provided to support national and international benchmarking of performance. Routine newsletters and reports on the study progress and other updates are to be developed by the global administrators and sent to the participating centres.

#### Data monitoring

There will be no routine onsite monitoring undertaken of the data entered. Participating clinics are not asked to store paper documents as source documents for data entered online. Hence, cross checks between data entered and source data is not possible. Online random spot-checks will be conducted on five percent of the data entered quarterly at each participating Cochlear P-IROS clinic by the global administration team.

The platform has been designed with inherent checks-of-response fields entered on eCRFs and automatically pending response types. The vast majority of responses on all forms are multiple choice, check box, radio buttons or pull-down response options to facilitate entry and reduce entry error. Minimal free-text response fields are included. The electronic registry platform operating the Cochlear P-IROS contains an inherent audit trail to trace all amendments made with each form, the investigator making the change and when changes are made. To avoid unnecessary changes, eCRFs are automatically locked upon access and data entry into the corresponding form at a subsequent assessment interval. Manual unlocking of these forms can be requested by the clinician to the Cochlear P-IROS global administrator.

#### Statistical analysis

A proposal for the statistical methods and data analysis plan for the assessment of Cochlear P-IROS hypotheses created by a consultant statistician is available as a separate report upon investigator’s request. Prospective, longitudinal studies, such as the Cochlear P-IROS, are especially powerful due to the repeated measures on participants. As such, relatively low numbers of observations may be adequate for most tests. A sample size of n = 50 was considered sufficiently sensitive to measure implant treatment effects assessed by the CAP-II, based on published literature. Current publications on paediatric cochlear implants lack sufficient detail on the SSQ-P or SSQ to generate an accurate power calculation for the sample sizes needed to find significant differences or changes; whilst CuHI-Qol is a completely novel outcome measure and, therefore, a sample size calculation is not currently possible.

It is also not possible to determine the actual number of patients that will be registered with the Cochlear P-IROS over time, as participation in the Cochlear P-IROS is voluntary for the clinic and the parent/caregiver/patient. Additionally, the parent/caregiver/patient may also cease to participate in the registry at any time. Nevertheless, the design of the database does not pose any constraint on the number of patients that may be enrolled over time, as it was developed with the aim to sustain data collection in the long-term. Large scale enrolment of patients in the range from 100 to 1000 or more on an annual basis is expected.

## Discussion

The Cochlear P-IROS provides a unique opportunity for improving the evidence base relating to outcomes achieved by patients with a permanent hearing impairment using implantable hearing devices. It removes barriers to participation from non-English speaking clinicians and patients by offering an easy-to-access, secure web platform with multiple language options and automated reports to support benchmarking activities. The registry is designed to collect clinical, demographic and patient-related outcomes data from newly implanted patients who are presented for routine intervention.

The Cochlear P-IROS web interface, as well as patient forms, have been translated into multiple languages in order to enable cross cultural data collection and subsequently cross cultural application of the interpreted outcomes. Thereby, the study reduces the potential risk of selection bias that may arise from exclusion of patients with a non-English speaking background. The Cochlear P-IROS design also minimises potential bias from recall errors, with a recall memory period of four weeks requested at each evaluation interval [57]. The authors, however, acknowledge that there may be a risk of emotional bias for the baseline evaluation time point. This is because the evaluation takes place part way through the two-part fitting of an implantable hearing device; that is, after the surgical placement of the internal implant but before activation of sound, with the fitting of the external sound processor.

The registry addresses industry-wide concerns around a lack of language-independent, standardised outcome measures for paediatric recipients of implantable hearing devices. To date, the wide variety of language-based, auditory-related outcome measures utilised in this patient population hinders effective meta-analysis [19]. Through the development of a new quality of life instrument, the CuHI-QoL, and the use of a range of standardised outcome measures (SSQ-P and CAP-II), Cochlear P-IROS aims to provide a homogeneous set of data for the comparison of benefit of implantable hearing devices for considerably larger numbers of patients that are more representative of the treated population.

The advantages of using questionnaires for subjective assessment is that it allows for a view to the benefits obtained post-implantation through the patient’s eyes or in the eyes of their parents, specifically demonstrating hearing benefits and additional hearing-related benefits. A further advantage, not specifically addressed in this paper is the ability to use validated translations of such questionnaires for collection and collation of qualitative patient-reported benefits across different languages, both pre and post-implant, longitudinally [19,9,39]. Comparison of auditory benefit data assessed and reported using local speech audiometry measures is both challenging, in view of the differences in materials and methods, and not recommended where equivalency in materials and measurements is unknown. The Cochlear P-IROS approach could foster not only consistency of data collected but also encourage the reporting of consistent evaluation methods. This makes it one step closer to the possible availability of published meta-analyses of collective standardised outcomes from patients using implantable hearing devices, which could potentially be used by regulators, health technology assessors and health service provision decision makers.

The Cochlear P-IROS may preclude the need for large local capital investment to design and implement a multi-centre web-based registry. The study provides the grounds for various hearing implant clinics to develop and own their own set of patient profiles, outcomes data and accordingly pursue their own research interests which may lead to scientific publications. Collaborative, multi-centre publications are especially encouraged to combine data collection efforts from different investigators, which may strengthen the potential power of the data reported and the interpretation of the conclusions drawn. The Cochlear P-IROS registry, therefore, provides a cost-effective method for interested parties to establish and invest in the outcomes of patients using implantable hearing devices in the long term, in a clinically feasible, broadly consistent and practically sustainable manner.

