##### Children using Hearing Implants Quality of Life (CuHI-QoL)

This is a new Quality of Life instrument designed for this study, developed to assess quality of life of patients using implantable hearing devices via parent proxy (A copy of this questionnaire is available electronically) (Additional file 1). Its aim is to assess the impact of implantable hearing devices on the quality of life of very young patients, their parents’ expectations and the wellbeing of the family over time. A review of published literature on available health-related, quality of life instruments, hearing-health assessments and questionnaires used in the paediatric population and administered via parent proxy was undertaken during the development of this new measure. Specifically, an evaluation of the most commonly assessed domains and evidence of the corresponding sensitivity of the existing measures for implant treatment effects was reviewed. Published researchers of subjective scales used in the hearing-implant field were consulted to help determine the most relevant domains, content, and construct for this tool [42-48]. The resulting 25-item parent-reported questionnaire is divided into three sections; 1) Parental Expectations, 2) Impact on the Family, and 3) Quality of Life of the Child. The 25 questions cover the following domains; self–reliance, wellbeing and happiness, social functioning, general functioning, parental stress, and family cohesion. The questionnaire has been piloted to assess the feasibility and practicality of its use in multiple cultural (i.e., English and Asian) and socio-economic settings by parents and providers before being introduced as a tool for use in the study. The CuHI-QoL instrument is currently being validated by researchers at the Department of Audiology and Speech Therapy, University of Melbourne, Australia. The validation study includes parents of children with a hearing impairment who use either hearing aids or cochlear implants, and normal-hearing peers.

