##### The SSQ-Parents’ version (SSQ-P)

The SSQ-P is available for response via parent proxy for enrolled patients aged four to 10 years at the time of implantation. Based on the original SSQ above, covering the same three domains, it was modified and shortened for administration as a self-assessment tool for parental proxy following observation of their child’s behaviour in various listening environments in their daily lives, as considered applicable [38]. The SSQ-P is not recommended for parental proxy of children less than age four years, as the developmental changes observed in these patients may confound the judgment and, subsequently, the measurement of intervention effect over time. The reasons include difficulties associated with accurately rating the performance of younger patients in questions such as, “following a group conversation” [38]. In the design of this questionnaire for use in non-English speaking countries, a validated translation process was employed (e.g., from English to Hindi and Hindi to English). Necessary cultural adaptations were also made as required (e.g., use of the term ‘motor scooter’ instead of a ‘lawn mower’ in India) through personal communications with [name] (University of New England, NSW, Australia), the co-developer of the original SSQ.

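### Raw mean CuHI-QoL in international benchmarking may mix language version with real country differences, because no cross-language score equivalence is described; the concern is weaker for the SSQ-P

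*Protocol article*

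**What the plan says.** All places are in the protocol article.

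- **Data outputs.** The automated reports give "mean CAP-II, mean SSQ-P and mean CuHI-QoL". The section continues: "Country and global summaries across these measures are also provided to support national and international benchmarking of performance". No caveat on comparability is attached.
- **Electronic case report forms.** To date "the case-report forms for patients have been translated into 22 languages".
- **CuHI-QoL section.** The instrument was designed for this study. It was piloted for feasibility and practicality in English and Asian settings. Of validation the section says: "The CuHI-QoL instrument is currently being validated by researchers". That study covers parents of hearing-aid users, cochlear implant users and normal-hearing peers. No comparison between language versions is mentioned.
- **SSQ-P section.** For non-English-speaking countries "a validated translation process was employed (e.g., from English to Hindi and Hindi to English"). The next sentence says: "Necessary cultural adaptations were also made as required". One example is given, from India, and the co-developer of the original SSQ was consulted.
- **CAP-II section.** The CAP, from which the CAP-II was extended, is described as independent of language.
- **Discussion.** Of results from local speech audiometry, not of questionnaires, the article says that comparison is "not recommended where equivalency in materials and measurements is unknown".
- **Table 1.** The CuHI-QoL is required at baseline and at 6, 12, 18 and 24 months, and is optional after that. The SSQ-P is optional throughout.
- **Study hypotheses.** The primary hypothesis (CAP-II), secondary hypothesis a (SSQ-P) and tertiary hypothesis a (CuHI-QoL) compare post-implant scores with the pre-implant baseline.

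**The concern.** A difference in country means on a translated questionnaire has at least two sources: a real difference between the children, and a difference in how the version or the respondents' habits place answers on the scale. Where language version and country go together, the means alone cannot separate the two. Adjusting for age, device or follow-up time does not help, because the offset belongs to the measuring tool and not to the case mix. Enrolling more children does not help either: it narrows the interval around a biased difference.

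The CuHI-QoL is the exposed measure. Its general validation is unfinished, and what is described does not address cross-language equivalence. A clinic or payer who sees one country's mean below another's may take it as a difference in outcome.

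**Working it through.** **1. Output against evidence.** The article plans country and global means for three measures.

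| Measure | Evidence on comparability across languages in the article |
|---|---|
| CAP-II | Parent scale described as language-independent |
| SSQ-P | Validated forward and back translation process; wording adapted with the co-developer of the original SSQ; no test of score equivalence described |
| CuHI-QoL | Feasibility pilot; validation in progress; no cross-language comparison described |

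A sound translation process supports linguistic equivalence: the items mean the same thing. Score equivalence is a further step: children in the same state receive the same score. The SSQ-P has stated support for the first. For the CuHI-QoL the article describes neither.

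**2. Levels against change.** Let a child's score be T + o, where T is the true state and o is the offset of the language version used.

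- Difference in levels between countries A and B: (T_A − T_B) + (o_A − o_B). The offset stays in.
- Change within a child from baseline (0) to follow-up (1): (T_1 + o) − (T_0 + o) = T_1 − T_0. The offset cancels if the same version is used throughout.

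The cancellation covers a constant offset only. If a version also stretches the scale by a factor b, the change becomes b(T_1 − T_0). Change is therefore much less exposed, but not immune.

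**3. Illustration of size.** The article has no figure to reproduce here: its sample size of 50 is for the CAP-II and has no bearing on this point. The offsets d (in SD units) and the numbers n per country are assumptions. With no true difference, equal groups and a two-sided 5% level:

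z = d / √(2/n); probability = Φ(z − 1.96) + Φ(−z − 1.96).

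For d = 0.2 and n = 100: √(2/100) = 0.1414, z = 1.414, and the probability is 0.293. For d = 0.2 and n = 500: √(2/500) = 0.0632, z = 3.162, and the probability is 0.885.

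| n per country | d = 0 | d = 0.1 | d = 0.2 | d = 0.3 |
|---|---|---|---|---|
| 50 | 5% | 8% | 17% | 32% |
| 100 | 5% | 11% | 29% | 56% |
| 250 | 5% | 20% | 61% | 92% |
| 500 | 5% | 35% | 89% | 99.7% |

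**4. How realistic are these n?** The Statistical analysis section expects 100 to 1000 or more patients a year across the whole registry. The Abstract names six countries already recruited and eight more intended. With an even split (an assumption):

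- Over six countries: 100/6 ≈ 17 to 1000/6 ≈ 167 per country per year.
- Over fourteen countries: 100/14 ≈ 7 to 1000/14 ≈ 71 per country per year.

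At 1000 a year, 500 per country would take about 3 years over six countries (500/167) or 7 years over fourteen (500/71). The lower rows of the table describe an accumulated registry, not its early reports.

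**The case against.** **Is this a self-contradiction?** A reader might infer that the article breaks its own rule in the Discussion, which calls a comparison "not recommended where equivalency in materials and measurements is unknown". The documents do not support that. The subject of the sentence is local speech audiometry, where clinics use different test materials, and the article offers common translated questionnaires as the alternative. Extending the caution to questionnaires is an analogy. The nearby mention of "the ability to use validated translations of such questionnaires" concerns qualitative benefits before and after implantation and is flagged as outside the paper's scope. It does not claim that country means are comparable.

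**Do only HUI3 translations count as validated?** A reader might infer this from the HUI3 section. It is wrong: the SSQ-P section states a validated translation process. The single example of adapted wording is a substitution meant to preserve meaning, and adaptation is documented for the SSQ-P only.

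**Are countries compared at all?** No objective or hypothesis compares countries, and no between-country significance test is planned. The reports are descriptive. This limits the damage and makes the percentages above an illustration of how easily an artefact could look real, not an error rate of the plan. It does not remove the point, because benchmarking is a comparison of levels.

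**Are language and country the same variable?** The article does not map its 22 languages to countries. Some countries may use several versions, and one version may serve several countries. The confounding is as strong as the overlap, which is not stated.

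**Is this only condensation?** Equivalence work may be described in the separate analysis report, and that cannot be ruled out. But the article itself states both the benchmarking output and the unfinished validation, so the point rests on what it says.

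**Conclusion.** The concern holds for the CuHI-QoL and, more weakly, for the SSQ-P. The plan releases country-level means for international benchmarking on an instrument whose validation is incomplete and whose scores are not shown to be equivalent across languages. Such differences may reflect wording or response style. The documents support no stronger word than may, because no offset is quantified and it could be zero.

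Under an assumed offset of 0.2 SD and no true difference, two countries would appear nominally different 29% of the time with 100 children each and 89% with 500 each. At 0.1 SD the figures are 11% and 35%. Both the offsets and the per-country numbers are assumptions.

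The harm is confined to comparing raw means between countries. Hypotheses that compare a child with that child's own baseline, including the CuHI-QoL hypothesis, are much less exposed, provided the language version stays the same for the child.

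**What to change.** Change the Data outputs section as follows, to apply until score equivalence across language versions is shown:

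- **CuHI-QoL:** in international summaries, show within-child change from the required baseline, or show means only within the same language version. Mark any raw cross-country means as not comparable.
- **SSQ-P:** keep the means, with a caveat that the translation process supports linguistic equivalence but that score equivalence has not been reported.
- **CAP-II:** keep as planned.

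The report needs to know which language version each form used. The article does not say whether this is stored; if it is not, one field is needed.

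The cost is a change to the report template and fewer direct level comparisons on these measures in early reports. Table 1 already requires the CuHI-QoL at baseline and at each follow-up to 24 months, so reporting change needs no new data collection. After 24 months the form is optional, so later change will rest on those who continue.
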